## Abstract

Auditory training is a technique that has demonstrated to be beneficial, improving auditory processing response as a supplement to hearing loss management. Recently, game-based training approaches have also demonstrated to increase the effect of traditional auditory training. Hence, the general aim of this work is to develop a game-based auditory discrimination training to enhance the auditory processing response and measure performance in comparison to traditional methods. The evaluation of the methods will be in three directions: (1) user experience, (2) perceptual and behavioral responses, and (3) neurophysiological performance. For this purpose, the project will be conducted as follows: (1) to develop and validate a game-based auditory discrimination training method in line with the usability level, and (2) to evaluate the auditory training in terms of method performance, and neurophysiological responses, before and after the procedure. The game-based auditory training will be focused on basic sound features discrimination tasks, which will be applied for 15 hours with 4 different modules. This will contribute to understand experience processes that yield to a better training performance.

## Introduction

According to the World Health Organization (WHO) [1], hearing loss is defined as the condition in which a person cannot hear as well as a person with normal hearing (thresholds are 20 dB HL or better on both ears). It is considered the most common and prevalent sensory deficit in the world [2,3] with estimates of 360 million people in 2022, and 466 million people in 2023. For 2030, it is expected to be the 7th most common disease [4]. Hearing loss severity is divided from moderate, severe moderate, severe or profound depending on hearing thresholds. According to the Rehabilitation National Institute in Mexico [5] in 2021, there existed about 2.3 million people with hearing loss in Mexico and it is estimated that 3 of each 1000 newborn have hearing loss [6]. Some of these numbers have not been updated since the recent pandemic situation (COVID-19). It is speculated that one of these virus sequels is hearing loss. Significant increase of people with hearing loss is suggested after COVID-19 pandemic [7].

There exist different solutions and treatments for people with hearing loss such as hearing aids, bone conduction headphones, surgeons, cochlear implants, and other interventions depending on the hearing loss type and severeness. Once hearing loss is correctly managed following best diagnosis and intervention practices [8,9], these solutions require adaptation processes and rehabilitation therapies to optimize their results. Sometimes, these alternatives may also be either uncomfortable or painful and their costs may be high for the low-income population. Non-invasive procedures and non-destructive means for hearing loss population are needed [3].

Auditory Training (AT) has shown to improve auditory processing conditions in hearing loss and normal hearing population through sessions of habilitation and rehabilitation [10–12]. However, neural plasticity changes may be not restored completely as that in normal hearing individuals [3]. AT has been mostly implemented through traditional methodologies and techniques, where experience-dependent performance is uncommonly considered, using not entertaining or engaging tools and schemes. Although, it has been demonstrated that higher success and achievement levels are related to higher levels of immersion [13] Indeed, some new digital tools have been already proposed to enhance user experience in AT. These proposals have designed for dichotic and speech.

The usage of computerized-based and game-based training tools can manage emerging population necessities and commodities favoring accessibility to healthcare technology. People can have complementary training at home, optimizing audiologists time and theirs own, and reducing hospitals and clinics saturation, satisfying solutions as person-centered tools for tele-audiology [14].

Although there are some types of hearing loss that are not reversible and cannot be healed or cured yet by a medical treatment, such as permanent hearing loss due to conductive or some sensorineural damage, there are some others such as some sensorineural, sudden and mild hearing loss that can be recovered to a certain level or can be treated with some other devices. All of them require adaptative processes to assimilate new auditory reality, such as AT. Taking care of hearing has never been so important as now. At present, prolonged exposure to environmental noise, overuse of earphones and new appearing diseases such as COVID-19, hearing has become a public health problem. Regular audiological check-ups, consciousness about high sound intensities exposure, avoidance of harmful substances, are some of the considerations for hearing healthcare.

Over the past 3 years, COVID-19 was spread over the world with more than 7 hundred million cases [15], developing a diversity of physiological reactions leaving a series of sequels, some of them still unknown. As was mentioned above, one speculated derivation from this virus is hearing loss, due to a strong infection, it can yield to sudden sensorineural hearing loss [16]. During this pandemic period, access to hospitals and clinic visits were limited. Even some of those people with audiological treatments that have been in therapy before 2020, had seldom follow-up sessions. Considering this, new audiological reality establishes two main challenges. One of them is to having better tools for auditory adaptative processes in rehabilitation, and second one is to develop tools that enhance engagement tasks and active involvement of users to obtain better training performance.

### State of the art

#### Computerized AT performance.

AT has been mostly applied since the beginning of early 2000s, in this brief review some of the most important and relevant studies and their results will be summarized to give a general idea of latest research and their highlights.

Two main assessments for AT performance have been conducted. The first one was to measure an improvement in auditory defined tasks after AT and an evaluation pre and post training to be compared through tasks’ results and behavioral tests. These tasks involve audiological assessments and specific training techniques in each study. The second assessment involves electrophysiological response before and after AT, mostly based on auditory evoked potentials (AEPs). Fewer cases evaluated the training performance by some other tests, including some of them the usability and validation of their methodology.

There has been studied the effects of AT in auditory response and perception through different means and different methodologies and it has been demonstrated the effectiveness to improve auditory skills such as general sensory, social and cognitive skills [17], of people with hearing impairment, intervention rehabilitation and auditory disorders. There is a broad literature on AT employing a variety of training skills for different populations [18,19]. One recent approach has been incorporated to evaluate interfaces usability and experience in the effects of AT [20]. The efficiency of this structure set, as mentioned by the authors, depended mainly on auditory experience. Auditory tasks and exercises, even the simplest ones, are influenced by high-level functions such as memory, motivation and decision-making [12].

Barton and Brewer [12] indicate the following principles as important to follow during AT:

Frequent, challenging and motivating.Diverse tasks to maintain motivation.Gradual in difficulty over time.Follow-up acquired responses (>70%).Monitored based on psychophysical, electrophysiological and questionnaire-based data.

It has also been demonstrated that long-term changes in auditory cortical neuronal single unit or population activity that is involved in sound acoustic experience mostly result from the differential engagement of similar neural mechanisms [21]. In this way, motivation and attention during activity has been measured through electrophysiological signal acquisition analyzing engagement index level beta/alpha correlation for sustained attention performances [22], confirming a relation between task engagement and alpha/beta rhythms.

#### AT and game-based training.

With the purpose of offering a better experience and motivation, game-based training approaches and computer-based AT have been little explored or have not always followed scientific guidelines for unbiased research. Gamification has enhanced engagement and learning, and studies about game-based tools and game element effects have reported an increase in user retention and other favorable results [23]. Research done at the beginning of 2010s has focused on offering computerized-based and digital tools for hearing and aural rehabilitation improving user accessibility and fitting new technology possibilities. Olson [24] provides review of specific computer and mobile-based AT programs considering their usefulness in patient centered care and self-management.

There have been some methodologies and developments to apply AT with computer or game-based approaches. For this research purpose, the three following approaches are described due to the similarity in methodology or evaluation.

One recent study by Stewart [25] tested auditory cognition and perception with 80 participants with a specific videogame experience, as well as visual reaction task, but performance of auditory tasks did not present significant benefits, suggested by visual environment interaction rather than auditory. Whitton tried to demonstrate that perception and learning on a computerized audio game can be developed after an eight-week AT program for the hearing-impaired population [13]. Whitton reported that after this time speech-in-noise intelligibility with conditions that challenges listening has improved about 25% and that control ability and game strategy predicted individual training improvement [26].

Tuz developed a computer-based auditory AT [20] evaluating 40 adults with hearing impairment proposing five levels of usability subscales: (1) ease of use, (2) comprehensibility, (3) design, (4) satisfaction and (5) motivation. They validated their development through the Software Usability Measurement Inventory (SUMI) and Computer Usability Satisfaction Questionnaires for usability evaluation purposes, in five main usability subscales. Later, they applied the computer-based AT evaluating nine auditory modules. Although their development and research were mainly focused in this first stage to design and validate the program, it addressed an antecedent in usability validation for AT resources, suggesting that validation obtained by both specialists and participants may be an indicator of retaining motivation of individuals.

One of the latest research projects studied learning transfer through an AT game for speech perception. Gamified mixed training approach was applied to college-aged with no hearing difficulties. Software training performance was evaluated across task progress, auditory perceptual outcomes, and cognitive outcomes, investigating the effectiveness of gamified AT on speech in competition and reporting improvement in working memory updating task [19]. Still, it was concluded that more research is required to understand which game elements these effects are dependent on as it is also suggested that game design elements motivation should be analyzed in specific contexts [27].

#### AT & auditory evoked potentials.

Since different techniques of AT have been developed, there has been various research to demonstrate the effectiveness of AT in electrophysiological measurements through AEP extraction and analysis.

Binaural AT effectiveness was evaluated comparing skills in three moments, before training, immediately after, and 3 months after. Participants 19–30 years old received training 30 min twice a week during 12–20 sessions. Long latency auditory evoked potentials (LLAEP), frequency following response and auditory brainstem response (ABR) were obtained showing subtle latency reduction in ABR components 3 months after AT and amplitude increase in left ear P3 component [28].

Another recent research measured auditory-based targeted cognitive training performance through mismatch negativity (MMN) and P3a components as neuromarkers of early auditory information processing. Auditory-based targeted cognitive training was implemented through exercises of auditory frequency discrimination. Training was implemented for 1 hr. just once and no significant changes were found between baseline and final auditory-based targeted cognitive training [29].

#### Aim.

In the light of the evidence, the aim of this research is to determine whether differences in user experience between the two systems; a game-based auditory discrimination training program and a non-game-based auditory discrimination training program, lead to differences in auditory discrimination perceptual, behavioral and electrophysiological performance within a normal-hearing population To meet this aim, the research will be conducted as follows:

To develop and validate a digital game-based auditory discrimination training tool.To develop a weekly program and to monitor key performance indicators (KPIs) in terms of time, accuracy and discrimination thresholds.To measure auditory processing improvement through perceptual, behavioral and electrophysiological tests comparing discrimination tasks’ performance before and after the use of auditory discrimination training system.

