## Methods

### Sample size, inclusion & exclusion criteria

Sample Size is determined by two means; literature has worked with sample sizes averages between 10–40 participants, due to the long training period and evaluation requirements [30,31]. Sample size was calculated determining F-tests family for ANOVA repeated measures between and within interactions, given a moderate effect size of 0.25, alpha error prob of 0.05 and power of 0.80, two groups and two measurements. Effect size was determined with related previous works, where effect sizes of behavioral auditory discrimination measurements are reported from moderate to large, based on Cohen’s d and Cohen’s f calculations [32–35]. Larger effects sizes have been suggested when individuals were submitted for first time to auditory devices [36].

G*Power 3.1 points a total sample size for both groups of 34. Considering two independent groups for auditory discrimination training (ADT) implementation, sample size for Group A (control), and Group B (experimental) will be equally distributed.

A total of 40 participants will be recruited and enrolled in the study, as described in Fig 1, predicting a sample rejection of ~10%. Each of them will be randomly assigned to one of two groups (control group or experimental group) depending on the training methodology they will receive. Sample size for each group (non-game-based ADT and game-based ADT) is 20 individuals each. Assignments of each participant will be randomized using simple randomization 1:1 allocation ratio to select the group for the training methodology, avoiding bias on trials.

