**Fig 3 pone.0313478.g003:**
[figure not shown]
Protocol steps. 1) Game-Based AT is first developed and validated through perceived usability evaluation questionnaires. 2) Assessments are done before and after AT is implemented for two sample groups. 3) Finally AT effectiveness is measured and compared through groups performance and AEPs.

The participant will be introduced to the study, explaining to them the informed consent and the confidentiality criteria. Participants will be given their audiometry results and a beginner game kit, also they will receive an online-shop gift card ($5-$25 us) if they finish the training levels satisfactorily, based on constant and consistent game playing, meaning they accomplish daily training and completely succeed in all training levels. Participants will also receive hearing health information after intervention and the option of scheduling a medical appointment with the otorhinolaryngologist and/or audiologist if they desire.

Auditory assessments will be conducted in noise-controlled rooms within university buildings or hospitals. Eligibility screen, informed consent and pure tone audiometry will be carried before allocation. Procedure to follow will be explained to them, beginning the pure-tone audiometry (air and bone) procedure. The participant will be indicated to raise the hand when they start to listen to the stimuli.

Then, they will be introduced to the electrode placements. Electrodes (Fz, F3, F4, Cz, C3, C4, T7 & T8) will be placed, and conductive gel will be applied to reduce the electrode-skin impedance. Calibrated headphones will be placed carefully. The participant will be asked to remain seated and still during evaluation. This process will be applied for the pre and post training assessment.

As shown in Fig 4. basal state will be recorded for 60 s in opened and closed eyes conditions. Then oddball paradigm will be used to assess auditory discrimination in pitch, intensity, duration and localization of the stimuli. P300 & Mismatch Negativity Potentials will be assessed by this paradigm in attentional and non-attentional conditions.

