### Expected outcomes & analysis

The primary outcome measures are related to neuro audiological changes in auditory processing. AEPs to be obtained are Mismatch Negativity and P3 components (continuous). Additionally, number of discrimination trials (discrete) will be registered. The secondary outcome measures are the in-game indicators such as time in each activity (continuous), accuracy (discrete) and attempts (discrete) to relate directly changes in audiological measures and game performance. The expected outcome of ADPQ is to increase the average score, that indicates a better perceived state and performance in auditory discrimination tasks that would be correlated with the in-game indicators and the electrophysiological measurements. The expected comparison outcome for AEP, it is expected an increase in evoked potentials amplitude and a decrease in latencies. For the in-game indicators it is expected to increase accuracy answers and decrease tasks’ solving time.

Once obtained and processed KPIs and discrimination threshold results, data will be analyzed with the following tools. Each of them will compare before and after auditory training KPIs and AEPs tests.

A 2-way analysis of variance (ANOVA) with repeated measures will be done considering the following factors.

For pre & post training measurements to determine individual performance of each methodology and contrast the improvement of each (within factors).For training group. Both methodologies have a similar distribution of activities to accomplish withing the training. Each group will be evaluated to determine if some activity yielded to a more significant difference in the overall performance (between factors).Finally, and mainly, for AT methodology groups to analyze and compare the final performance between the game-based experimental groups and the non-game-based control group and conclude if there is a significant difference between them.

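### Before-to-after change in two trained arms cannot show that either method works; only the between-arm difference in change can carry a confirmatory claim

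*Protocol article*

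**What the plan says.** The protocol article asks two kinds of question.

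- **Between arms.** The Aim section opens with "the aim of this research is to determine whether differences in user experience between the two systems" lead to differences in performance. The sample size section powers the matching test, described as "F-tests family for ANOVA repeated measures between and within interactions". Expected outcomes & analysis marks the contrast between the two methods as the main one.
- **Within arms.** The third objective in the Aim section is "To measure auditory processing improvement through perceptual, behavioral and electrophysiological tests comparing discrimination tasks’ performance before and after the use of auditory discrimination training system". The first factor listed under Expected outcomes & analysis is "For pre & post training measurements to determine individual performance of each methodology and contrast the improvement of each (within factors". The Fig 3 caption (Study design & setting) ends: "Finally AT effectiveness is measured and compared through groups performance and AEPs". The stated expectations (larger evoked potential amplitudes, shorter latencies, a higher questionnaire average, better accuracy, shorter solving times) are all changes over time. None gives a direction between arms.

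On design, AT experimental design gives both groups 15 hours on the same four modules: pitch, intensity, duration and localization. Study design & setting applies the same EEG procedure before and after training. The list of conditions that could bias the primary outcomes has three entries: discrimination performance, hearing health and simultaneous training. Retest, practice and habituation are not among them. The Discussion leaves additional measurement times to future research.

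**The concern.** Group A is called the control, but it is trained, so it controls for the game elements and not for time or repeated testing. With one assessment before and one after, the time effect in either arm is the sum of what training did and what a second sitting did: familiarity with the oddball task, habituation to the tones, ease with the recording set-up. Nothing described in the article separates these parts.

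At stake is what may be concluded. A significant time effect could be taken to show that auditory training improves auditory processing. If both arms change by the same amount, the data are equally compatible with two effective methods and with two ineffective methods plus a retest effect.

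**Working it through.** **1. The plan's own figure.** The inputs in the sample size section are "given a moderate effect size of 0.25, alpha error prob of 0.05 and power of 0.80, two groups and two measurements". For the interaction in a repeated-measures ANOVA, λ = f²·N·m/(1−ρ), with df1 = (k−1)(m−1) and df2 = (N−k)(m−1). The correlation ρ between the two measurements is not stated; 0.5 is assumed.

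- N = 34: λ = 0.0625 × 34 × 2 / 0.5 = 8.5, df = 1 and 32, power 0.807. This matches "G*Power 3.1 points a total sample size for both groups of 34".
- N = 40: λ = 0.0625 × 40 × 2 / 0.5 = 10, power 0.869.
- Range for the unstated ρ: N = 66 at ρ = 0, 46 at 0.3, 22 at 0.7, 16 at 0.8.

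The powered test is therefore the between-arm difference in change.

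**2. What each test estimates.** Let training move arm A by τA and arm B by τB, and let a second sitting move both by δ.

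- Change within arm A: τA + δ. Change within arm B: τB + δ.
- Pooled time effect: (τA + τB)/2 + δ.
- Group-by-time interaction: (τB + δ) − (τA + δ) = τB − τA.

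The shift δ stays in every before/after estimate and cancels from the interaction when it is equal in both arms.

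**3. Illustration of size.** The documents give no value for δ, so 0.2, 0.3 and 0.5 SD of a single measurement are assumptions. Set τA = τB = 0. The SD of the change score is √(2(1−ρ)) in those units, which is 1 at ρ = 0.5. The noncentrality is then δ√20 in one arm (0.89, 1.34, 2.24) and δ√40 pooled (1.26, 1.90, 3.16). Two-sided tests at 0.05, 40,000 simulated trials per setting:

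| δ | One arm, n=20 | Time effect pooled, n=40 | Interaction |
|---|---|---|---|
| 0 | 4.9% | 5.0% | 4.8% |
| 0.2 | 13.4% | 23.2% | 4.9% |
| 0.3 | 24.6% | 45.4% | 4.8% |
| 0.5 | 56.7% | 87.1% | 5.1% |

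Noncentral t probabilities agree: 24.7% and 56.5% for one arm, and 45.7% and 86.9% for n=40, at 0.3 and 0.5 SD.

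**4. Sensitivity.** With 17 completers per arm (the calculated total of 34) and ρ = 0.5, the one-arm figures are 12%, 21% and 49%, and the pooled figures 21%, 40% and 81%. With 20 per arm and ρ = 0.7, they are 19%, 37% and 79%, and 36%, 66% and 98%. The interaction stays near 5% throughout.

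**The case against.** The strongest reply is that the trial's question is comparative. The before/after objective is one of three steps toward a between-system aim, and measuring before and after is how a difference in change is obtained. The Fig 3 caption says effectiveness is compared as well as measured, and the within-factor item also speaks of contrasting the two improvements. An active comparator suits this question, and no trial with two active arms can separate both working from neither working.

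Most of this stands. A reader might infer that the randomised comparison or the total of 34 is compromised. The documents do not support that: the interaction is unaffected by a shift common to both arms, and 34 reproduces. A reader might also infer that the protocol plans to report a time effect as proof that training works; no sentence says so. Three further limits apply:

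- The retest shifts are hypothetical.
- Habituation could work against the expected rise in amplitude, so the before/after estimate need not flatter training.
- That the questionnaire is taken at both assessments is an inference. Materials says only that it is used during and after each acoustic feature, partly to reduce bias from the participant's state. That is some protection against state effects, but not against retest.

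What the reply does not remove is the wording that assigns a conclusion to the within factor: it is to determine the performance of each method. Ranking the between-arm contrast as the main one leaves that conclusion in place. Nor is this detail left to an analysis plan, because the objective, the arms, the assessment times and the reading of the within factor are all fixed in this article.

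**Conclusion.** The point holds as a limit on interpretation. The before-to-after change mixes training, retest and habituation in unknown proportion and direction, so it cannot support a claim that either method improves auditory processing. In the illustration, a test with a nominal 5% rate is significant in about 13% to 57% of trials within an arm and 23% to 87% pooled, for assumed shifts of 0.2 to 0.5 SD. These figures show sensitivity to an unknown quantity. They rest on the assumed shifts, on ρ = 0.5, on no training effect and on the same shift in both arms, and they are not estimates for this trial.

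The absence of an untrained arm or repeat baseline is judged from the text and captions, since the figures are not shown. These consistently describe two trained groups assessed before and after.

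**What to change.** - In Expected outcomes & analysis, name the group-by-time interaction (the between-arm difference in before-to-after change) as the only confirmatory test. This matches the sample size calculation. It also settles the main contrast, which is now worded in terms of final performance.
- In the third objective of the Aim section, the Fig 3 caption and the within-factor item, label within-arm change as descriptive: change over the training period, including retest effects.
- State that equal change in both arms will not be read as evidence that either method is effective.

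This needs no added participants, visits or procedures, and the sample size stays as it is. The downside is a narrower claim: the trial could say whether game-based training changes outcomes more than non-game-based training, but not whether either works.

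If the investigators want the wider claim, the design itself would have to change, for example with a test-only arm or a repeat baseline. For scale only, a three-arm interaction test at f = 0.25 and assumed ρ = 0.5 needs 42 completers (14 per arm, power 0.803) against 34 for two arms.
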